#### 2.5.2. Study Arms: Intervention—Inhaled Sedation with Sevoflurane

Sevoflurane is vaporized via the miniaturized Anesthesia Conserving Device (Sedaconda ACD-S, Sedana Medical, Danderyd, Sweden), which is placed between the endotracheal tube and the Y-piece of the ventilator breathing circuit. The residual expired gas is scavenged following the manufacturer’s instructions using an active carbon filter (Flurabsorb, Sedana Medical, Danderyd, Sweden) [1]. As recommended by the manufacturer, Sedaconda ACD is replaced every 24 h and removed from the breathing circuit as soon as inhaled sedation is interrupted and for spontaneous breathing trials. Sevoflurane administration is interrupted, and the Sedaconda ACD-S removed from the breathing circuit, if severe acidemia (pH < 7.15) is present, in the absence of metabolic acidosis and despite tidal volume and/or respiratory rate increase, or if malignant hyperthermia or a bronchopleural fistula that is persistent despite drainage (to limit room exposure) develops. In these situations, sedation is switched to a strategy of intravenous propofol.

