#### 2.5.3. Study Arms: Control—Intravenous Sedation with Propofol

Propofol is administered via continuous intravenous infusion, as routinely used in participating ICUs. Propofol is interrupted if propofol-related infusion syndrome develops; in these cases, management and the choice of sedative agent(s) is as per the treating clinicians.

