#### 2.5.4. Common Strategies for Both Groups

Upon randomization, deep sedation is protocolized (Richmond Agitation-Sedation Scale (RASS) −4 to −5) and combined with the neuromuscular blockade (continuous infusion of cisatracurium besylate for a maximum of 48 h) in both groups. The neuromuscular blockade is continued until PaO_2_/FiO_2_ exceeds 150 mmHg for 4 h with FiO_2_ < 0.6 [21,23,24]; then, light sedation is targeted (RASS 0 to −1), with prompt sedation interruption whenever possible. In both arms, patients receive the allocated sedation strategy from randomization until sedation can be interrupted or until day 7, whichever occurs first. When sedation is required again within 7 days after randomization, the sedative agent to use is based on the randomization arm; after day 7, decisions on sedation are as per the treating clinicians. If the bispectral index (BIS^®^, Aspect Medical Systems Inc., Norwood, MA, USA) is available, the level of sedation under the neuromuscular blockade can be titrated and monitored using the BIS^®^, with a targeted value of 40–50 [14]. Pain management is conducted as per clinical teams, within a strategy of analgesia-first sedation, including frequent pain assessment with the behavioral pain scale (BPS); opioids agents, if needed, are those routinely used in participating centers.

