
**Table 3 jcm-11-02796-t003:** SESAR trial populations for primary, key secondary, secondary, and subgroup analyses.

Intention-to-treat population	All randomized patients except those who withdraw their consent for the use of data.
Per-protocol population #1	All randomized patients except patients having one or more major protocol violations defined as: Inhaled sevoflurane not administered in patients randomly allocated to the intervention arm *OR* 2. Inhaled sevoflurane not administered during the whole duration of sedation (within a maximum of 7 days from randomization) in patients randomly allocated to the intervention arm *OR* 3. Monitoring revealed that a tidal volume higher than 8 mL/kg PBW was applied *OR* 4. Monitoring revealed that one or more inclusion or exclusion criteria were violated *OR* 5. Patients withdrawn from the protocol because the patient would have withdrawn consent
Per-protocol population #2	All randomized patients except patients having one or more major protocol violations defined as: Inhaled sevoflurane was not administered in patients randomly allocated to the intervention arm *OR* 2. Inhaled sevoflurane was not administered during the whole duration of sedation (within a maximum of 7 days from randomization) in patients randomly allocated to the intervention arm
Subgroup populations	Patients with shock (defined as the need for intravenous vasopressor infusion to maintain arterial pressure) at randomization Patients with pre-randomization PaO_2_/FiO_2_ <100 mmHg Pre-randomization presence vs. absence of suspected COVID-19 Patients with hypoinflammatory versus hyperinflammatory phenotypes at randomization Patients with higher versus lower degrees of lung epithelial injury at randomization, as assessed by plasma sRAGE (thresholds to be determined according to univariate analyses and clinical relevance) Patients with higher versus lower degrees of lung endothelial injury at randomization, as assessed by baseline plasma ANG-2 (thresholds to be determined according to univariate analyses and clinical relevance) Patients with focal versus nonfocal ARDS at baseline, as assessed by lung CT-scan, chest radiograph, or bedside lung ultrasound (if available) Patients treated with lower (5–10 cmH_2_O), moderate (11–15 cmH_2_O), or higher (>15 cmH_2_O) levels of PEEP during the first 3 days after enrollment

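### Both per-protocol populations check adherence to the allocated sedative in the sevoflurane arm only, and count a switch that the protocol orders as a violation

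*Protocol article*

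**What the plan says.** Table 3 of the protocol article defines two per-protocol populations by listing the major violations that exclude a patient.

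- **Sedative criteria, in both populations.** A patient is excluded if sevoflurane was never given, or if it was "not administered during the whole duration of sedation (within a maximum of 7 days from randomization) in patients randomly allocated to the intervention arm". Each criterion is restricted to those allocated to sevoflurane.
- **Other criteria, in population #1 only.** These cover tidal volume ("Monitoring revealed that a tidal volume higher than 8 mL/kg PBW was applied"), breaches of eligibility and withdrawn consent. They are not limited to one arm.
- **Population #2** has only the two sedative criteria.

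The treatment sections read differently. Section 2.5.4 sets a common duty: "In both arms, patients receive the allocated sedation strategy from randomization until sedation can be interrupted or until day 7". Section 2.5.2 lists situations in which sevoflurane must stop. One is given as "Sevoflurane administration is interrupted, and the Sedaconda ACD-S removed from the breathing circuit, if severe acidemia (pH < 7.15) is present", with qualifiers on metabolic acidosis and ventilator adjustment; the others are malignant hyperthermia and a persistent bronchopleural fistula. It then states: "In these situations, sedation is switched to a strategy of intravenous propofol". Section 2.5.3 has a control-arm counterpart: "Propofol is interrupted if propofol-related infusion syndrome develops; in these cases, management and the choice of sedative agent(s) is as per the treating clinicians".

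Section 2.8.3 makes intention-to-treat the primary analysis and plans per-protocol analyses of the primary and secondary outcomes after it.

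**The concern.** Two features of Table 3 do not fit the rest of the protocol.

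First, the duty to follow the allocated sedation strategy applies to both arms, but departures lead to exclusion in one arm only. A control patient who never received propofol, stopped it or was given sevoflurane stays in.

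Second, a sevoflurane patient switched to propofol under section 2.5.2 has followed the protocol, yet fails the whole-duration criterion and is labelled a major violator. A control patient whose propofol is interrupted under section 2.5.3 is kept.

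Exclusion from the sevoflurane arm thus depends on events after randomization, some of them severe complications, with no matching exclusion among controls. At stake is whether the per-protocol results for ventilator-free days to day 28 (VFD28), 90-day survival and mortality can support the intention-to-treat result, or whether they partly reflect who was removed.

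**Working it through.** **1. The rules side by side**

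| Situation | Treatment sections | Table 3 |
|---|---|---|
| Sevoflurane patient never given sevoflurane | Departure (2.5.4) | Excluded |
| Sevoflurane patient switched for a listed reason | Ordered (2.5.2) | Excluded, no exemption |
| Control patient never given propofol | Departure (2.5.4) | Kept |
| Control patient given sevoflurane | Departure (2.5.4), unless chosen after an interruption under 2.5.3 | Kept |
| Control patient with propofol interrupted for infusion syndrome | Ordered (2.5.3) | Kept |

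Kept here means not excluded by any sedative criterion.

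**2. The plan's own figure**

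The only related number is the power in section 2.8.4: 350 per arm, difference 2 days, SD 8, two-sided 5%. SE = 8 × √(2/350) = 0.605. Power = Φ(2/0.605 − 1.96) = Φ(1.35) ≈ 91%, which agrees with the stated >80%. The article gives no figure for the per-protocol sets.

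**3. Size of a one-arm exclusion when there is no true effect**

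Inputs:
- Overall 28-day mortality 32.5%, the midpoint of the 30–35% in section 2.8.4.
- Overall mean VFD28 of 9 days (assumed).
- Among those excluded, mortality 45–60% and mean VFD28 5.5 down to 4 days (assumed).
- Fraction f of the sevoflurane arm excluded: 5%, 10% or 20% (assumed).

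Remaining mortality = (0.325 − f × m)/(1 − f). Remaining VFD28 = (9 − f × v)/(1 − f).

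For f = 10%, mortality is (0.325 − 0.045)/0.9 = 31.1% to (0.325 − 0.060)/0.9 = 29.4%. VFD28 is (9 − 0.55)/0.9 = 9.39 to (9 − 0.40)/0.9 = 9.56 days.

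| f | Remaining mortality | Spurious gain, points | Spurious gain, VFD28 days |
|---|---|---|---|
| 5% | 31.8% to 31.1% | 0.7 to 1.4 | 0.18 to 0.26 |
| 10% | 31.1% to 29.4% | 1.4 to 3.1 | 0.39 to 0.56 |
| 20% | 29.4% to 25.6% | 3.1 to 6.9 | 0.88 to 1.25 |

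**4. Effect on false findings**

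Let g be the deficit in mean VFD28 of the excluded patients. The shift is f × g/(1 − f). With SD 8, SE = 8 × √(1/[350(1 − f)] + 1/350), and the chance of a false finding for sevoflurane is 1 − Φ(1.96 − shift/SE), nominally 2.5%. This is a simple z-test, not the planned gamma-mixture model. Here g is taken over a wider assumed range, 3 to 8 days.

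| f | Shift, days | False finding for sevoflurane |
|---|---|---|
| 5% | 0.16 to 0.42 | 4.4% to 10.2% |
| 10% | 0.33 to 0.89 | 7.7% to 29.8% |
| 20% | 0.75 to 2.00 | 21.5% to 87.7% |

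If the excluded patients did 3 days better than average, the shifts become −0.16, −0.33 and −0.75 days.

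**5. With a symmetric rule**

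If the same rule removed the same fraction of similar patients from both arms, the shift would be zero. Patients kept because their switch was ordered contribute no shift.

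**The case against.** The strongest reply is that little depends on these analyses. The primary analysis is intention-to-treat, the question is superiority, and the Discussion ties its conclusion to VFD28 or 90-day survival without mentioning per-protocol results. That stands, and it limits the severity.

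A reader might infer more than the documents support, in four ways.

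- **That the bias must favour sevoflurane.** The ordered switches follow severe complications, and longer or repeated sedation gives more chances to fail the whole-duration criterion, so this is the likelier direction. But the prognosis of patients never started on sevoflurane is unknown, and patients who die early while still on it are retained. Keeping control patients who crossed over would dilute a true benefit and causes no shift under no effect.
- **That exclusions of 10–20% should be expected.** The switch triggers are narrow, and the Discussion puts malignant hyperthermia at 1 in 50,000 to 100,000. No exclusion rate is given.
- **That harm would be hidden.** Severe hypercapnic acidosis, malignant hyperthermia and persistent fistula are safety outcomes in section 2.7.6 and reportable events in section 2.8.1. The per-protocol analyses are planned for primary and secondary outcomes, and Table 2 lists safety outcomes separately.
- **That the tidal-volume criterion shares the defect.** It is not limited to one arm, and it marks a departure from the range in section 2.5.4. Nothing says that the response to acidemia goes above that range.

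None of this answers the one-sided wording or the missing exemption. Table 3 states the rule explicitly, so this is not a detail left to the analysis plan.

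**Conclusion.** The point holds for adherence to the allocated sedative. In both per-protocol populations that adherence is judged only in the sevoflurane arm, and Table 3 conflicts with section 2.5.2 by treating an ordered switch as a major violation. Population #2 keeps every control patient. In population #1 the one-arm description applies to the two sedative criteria and not to the other three.

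The supportive comparisons of the primary and secondary outcomes are therefore not like with like. A bias towards sevoflurane is probable but not established. Its size could run from a small fraction of a day to a sizeable part of the 2-day design effect, depending entirely on the assumed exclusion rate and prognosis.

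Severity is moderate: the intention-to-treat result, its power and its type I error are untouched.

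**What to change.** In Table 3, define adherence to the allocated sedation strategy in the same terms for both arms: the allocated strategy started, and used whenever sedation was needed up to day 7. Count interruptions and switches ordered by sections 2.5.2 and 2.5.3 as adherent. This reconciles Table 3 with sections 2.5.2, 2.5.3 and 2.5.4. It concerns the analysis sets only and leaves the clinical rules as they are. The tidal-volume criterion can stay as written.

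Report the number and reasons for exclusion by arm. A symmetric definition still conditions on events after randomization, so these analyses should remain supportive.

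The cost is a wording change, tabulation of sedative exposure in the control arm, and a smaller control per-protocol set.
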